**Methods/design:**

Thirty ambulant PPS patients will be recruited in Switzerland. Patients will be randomly allocated to one of the two arms of the study (placebo:verum 1:1). After a 24-week run-in phase to observe natural disease history and progression, participants will be treated either with L-citrulline or placebo for 24 weeks. The primary endpoint is change in the 6-min Walking Distance Test. Secondary endpoints will include motor function measure, quantitative muscle force, quantitative muscle magnetic resonance imaging and magnetic resonance spectroscopy and serum biomarker laboratory analysis

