**Discussion:**

The aim of this phase IIa trial is to determine if treatment with L-citrulline shows a positive effect on clinical function and paraclinical biomarkers in PPS. If treatment with L-citrulline shows positive effects, this might represent a cost-efficient symptomatic therapy for PPS patients.

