##### Change of serum concentrations for markers of muscle necrosis (creatine kinase), oxidative stress (8OHDG, carbonylated proteins 4-Hydroxynonenal (4-HNE)), nitrosative stress (nitrotyrosine, cGMP), and mitochondrial-related genes (*Citratsynthase*, *Cytochrome C oxidase subunit 1*, *Succinate dehydrogenase subunit A*)

Our treatment aims at a stimulation of NO concentrations measured by indirect markers (nitrotyrosine, cGMP), an improvement of the muscular energy situation (citratsynthase, cytochrome C oxidase subunit 1, succinate dehydrogenase subunit A) with reduction of oxidative stress (8OHDG in urine, carbonylated proteins) and a slowing of muscle degeneration (levels of creatine kinase, transaminases, alkaline phosphatase).

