### Statistics

The full analysis set (FAS) consists of all patients who are randomised and for whom a baseline measurement of the primary endpoint is available. The intention-to-treat (ITT) set is a subset of the FAS that consists of all patients for whom there is a follow-up measurement of the primary endpoint. According to the ITT principle, each patient will be analysed according to the treatment that they are randomly allocated to. The per-protocol (PP) set is a subset of the ITT set that consists of all patients with complete follow-up measurements of the primary endpoint. Each patient will be analysed according to the treatment that they actually receive.

An ANCOVA will be used for the primary analysis. The response variable is the 6MWD after the 24-week treatment period (follow-up). The explanatory variables are the 6MWD at the onset of the treatment period (baseline) and the group (placebo versus verum). The model estimates will be presented together with 95% confidence intervals and *p* values with respect to the null hypothesis that the corresponding estimate has a value of 0. The analysis will be performed on the ITT set. The analysis will be repeated on the PP set and compared to the ITT analysis as a sensitivity analysis.

Following the analysis of the primary endpoint, the secondary endpoints will be analysed as outlined above for the primary endpoint.

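### Secondary endpoints inherit an analysis set defined by the walk test; the scale of concentration markers and the status of muscle force also need fixing

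*Protocol article*

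**What the plan says.** All references are to the protocol article.

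- **Analysis sets (Statistics).** The full analysis set (FAS) is "all patients who are randomised and for whom a baseline measurement of the primary endpoint is available". The ITT set is the part of the FAS that "consists of all patients for whom there is a follow-up measurement of the primary endpoint". The PP set is the part of the ITT set with complete follow-up of that same endpoint. The primary endpoint is the 6MWD, so all three sets depend on the walk test. The main analysis uses the ITT set and is repeated on the PP set.
- **Model (Statistics).** ANCOVA of the follow-up value on the value at the start of treatment and group, with 95% confidence intervals and p-values. No transformation is mentioned.
- **Secondary endpoints (Statistics).** After the primary analysis, "the secondary endpoints will be analysed as outlined above for the primary endpoint". No exception is given.
- **Secondary outcome measures.** The headings are MFM total score, quantitative MRI with spectroscopy, and "Change of serum concentrations for markers of muscle necrosis (creatine kinase), oxidative stress", followed by nitrosative stress and mitochondrial markers.
- **Muscle force.** The abstract states: "Secondary endpoints will include motor function measure, quantitative muscle force, quantitative muscle magnetic resonance imaging". The outcome section instead puts quantitative muscle testing under auxiliary outcome measures.

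**The concern.** A rule written for the walk test does not transfer intact to an MRI, a blood marker or a motor score.

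- **Set.** Whether a patient's week-48 MRI counts would depend on whether that patient walked. A missing walk may be related to how the patient is doing: eligibility requires only 150 m, and the article calls the disease progressive. The inherited set could therefore discard valid data, and not at random.
- **Scale.** Biological concentrations cannot be negative and may be right-skewed. If they are, one or two high values can dominate an untransformed ANCOVA of about 25 patients and hide an effect on the markers meant to show the mechanism.
- **Muscle force.** The Statistics section gives a rule for secondary endpoints only. The label therefore decides whether muscle force receives the ANCOVA and a p-value at all.

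**Working it through.** **1. The plan's own figure.** Sample size estimation asks for 28 recruits to obtain 25 evaluable at 10% dropout. 25 / (1 − 0.10) = 27.8, rounded up to 28, so the figure reproduces. The planned enrolment is 30, and 30 × 0.90 = 27.

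**2. Who is in the set.** Study procedure lists the 6MWD at weeks 36 and 48 on treatment, MFM and blood at weeks 36 and 48, and MRI at week 48. These are separate procedures. Taking week-48 MRI as the example:

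| Follow-up 6MWD | Week-48 MRI | ITT, if any follow-up walk counts | ITT, if the week-48 walk is needed |
|---|---|---|---|
| week 48 present | present | analysed | analysed |
| week 36 only | present | analysed | dropped |
| none | present | dropped | dropped |
| week 48 present | absent | in the set, no response | in the set, no response |

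The third row is lost on either reading. The second is lost on one reading, and from the PP set if complete follow-up means both visits.

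**3. How many.** If the assumed dropouts are the patients without a follow-up 6MWD, the most that could be regained is 28 − 25 = 3 (or 30 − 27 = 3), and only those who still had the other measurement. If all 3 were regained, standard errors would change by a factor of about √(25/28) = 0.945, a gain of at most about 5%. The selection matters more than the precision.

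**4. Scale.** The article gives no marker distributions, so every input here is an assumption: log-normal marker, 12 against 13 patients, true ratio of geometric means 0.6, two-sided 5% test, SD and baseline-to-follow-up correlation on the log scale as shown. Each simulated trial was analysed by ANCOVA on untransformed and on log values (10,000 trials per setting; 4,000 at correlation 0.85).

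| SD(log) | Correlation | Power, raw | Power, log | Loss (points) |
|---|---|---|---|---|
| 0.3 | 0.5 | 99% | 100% | under 1 |
| 0.5 | 0.5 | 73% | 79% | 6 |
| 0.5 | 0.85 | 98% | 99% | 1 |
| 0.6 | 0.5 | 54% | 63% | 8 |
| 0.6 | 0.8 | 83% | 91% | 8 |
| 0.8 | 0.5 | 30% | 40% | 11 |
| 0.8 | 0.8 | 52% | 70% | 18 |
| 0.8 | 0.85 | 62% | 80% | 18 |
| 1.0 | 0.5 | 19% | 28% | 9 |
| 1.0 | 0.8 | 31% | 51% | 19 |
| 1.0 | 0.85 | 38% | 62% | 24 |

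Losses are taken before rounding where unrounded values were available. With no true effect, raw-scale rejection ran from 3.9% to 5.2% for SD(log) 0.3 to 1.0 and correlations 0.5 and 0.8. The type I error is therefore not inflated.

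**5. Muscle force.** Abstract: secondary. Outcome section: auxiliary. No arithmetic is needed; the two passages cannot both stand.

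**The case against.** **The set may be meant endpoint by endpoint.** To apply the rule to MRI, a reader must already replace 6MWD by the MRI value as response and covariate, so the set could be read the same way. That is a fair guess at intent. But ITT and PP are named sets with one fixed definition, and the text does not say that they change with the endpoint. It is also fair that the week-36 walk may keep some patients in. This reduces the number affected but does not remove the problem.

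**Scale is left open, not fixed wrongly.** The article never says raw scale, describes no distribution, and may leave transformation to an analysis plan that is not shown. Skewness is an outside assumption, and the secondary endpoints were never powered. The markers are also not all serum concentrations: the text places 8OHDG in urine and heads the mitochondrial markers as genes. All of this stands, so the scale point is an improvement with a conditional benefit.

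**A stronger reading: uncontrolled multiplicity.** A reader might count MFM (1), T2 and lipid (2), PCr, ATP and pH (3) and eight laboratory markers, 14 in all. At an assumed 0.05 each, 1 − 0.95^14 = 51% for at least one false positive. The stated aim, to learn whether treatment "shows a positive effect on clinical function and paraclinical biomarkers in PPS", might seem to rest on those tests. The document does not support calling this an error. It has one primary endpoint in a phase IIa trial and makes no confirmatory claim for the secondaries, so the primary type I error is untouched. It lists three secondary headings and does not fix the number of tests. The 51% also needs independence; at assumed correlations of 0.3 to 0.7 it falls to about 44% to 25%.

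**Conclusion.** The concern holds in limited form.

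- **Analysis set: the main point.** It rests on the article's own definitions. As written, patients can be excluded from MRI, MFM and blood analyses for lack of a walk test. On the plan's dropout assumption at most 3 patients are involved, probably fewer, in a trial expecting about 25 evaluable.
- **Log scale: worthwhile but conditional.** If the markers are right-skewed, the cost of untransformed ANCOVA is power, not false positives. At a ratio of 0.6 and correlation 0.80 to 0.85, it is about 18 to 24 points at SD(log) 0.8 to 1.0. At correlation 0.5 it is about 9 to 11 points there. It is close to nil at SD(log) 0.3, and 1 to 6 points at 0.5 depending on the correlation.
- **Muscle force: a plain contradiction** between abstract and outcome section.

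It would be wrong to infer that the primary analysis is compromised, that the secondary tests are invalid, or that a multiplicity adjustment is owed.

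**What to change.** 1. **Set.** State that each secondary endpoint is analysed in all randomised patients, as allocated, who have baseline and follow-up data for that endpoint, whether or not a follow-up 6MWD exists.
2. **Scale.** Prespecify that positive concentration markers (for example creatine kinase, 8OHDG, 4-HNE, nitrotyrosine and cGMP) are analysed as log follow-up on log week-24 value and group, and reported as ratios with 95% confidence intervals. Fix this before unblinding so that the choice cannot depend on the results.
3. **Muscle force.** Reconcile the abstract with the outcome section, and state which analysis applies to it.
4. **Optional.** One sentence saying that secondary p-values are nominal.

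The cost is wording only; visits, data collection and sample size do not change. The small downside is that marker effects are read as ratios, and that numbers of patients may differ between endpoints and should be shown beside each result.

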### Quality control

Monitoring of the study will be performed by an independent person (KMS Monitoring, Zug). All inclusion and exclusion criteria will be checked, whether the data have been recorded correctly in the CRF, whether the drug accountability is correct and whether any serious adverse events (SAEs) have occurred during the study.

### Ethical considerations

PPS is a serious progressive neuromuscular disease with no therapy so far. Affected patients suffer from severe impairment that justifies an attempt to improve this condition using an almost side-effect-free treatment.

The participation in this study is voluntary. If the patients do not want to participate, they will not experience any disadvantages concerning any further medical treatment. The same applies if the patients withdraw the consent at a later time point. They have this possibility at any time. Possible withdrawal of consent from the study can occur without giving any reason. In case of withdrawal the data collected until this time point will be used and the samples (blood) collected in the context of the study will be destroyed. In case of withdrawal the patient will undergo a final visit for a medical examination for his own safety.

A placebo group is necessary to demonstrate the efficacy of the used medication (CIT) and to exclude a possible placebo effect.

There is a great potential that positive results of this study could lead to other large multicenter trials. Furthermore, if we can show an effect of CIT on muscle function, this will be a major breakthrough and mean a better symptomatic treatment of the muscle degeneration that occurs in PPS.

## Discussion

The aim of this investigator-initiated, randomised, placebo-controlled, double-blind, phase IIa trial is to examine whether treatment with CIT has a beneficial effect on clinical muscle function and fatigue and on the surrogate biomarkers that assess muscle ATP production and mitochondrial function in PPS. If this turns out to be the case, a cost-effective, symptomatic therapy with CIT could be available for these patients.

As PPS is a very heterogeneous disease, all patients will undergo a 24-week observational (untreated) period to observe the natural history of the disease. For the primary endpoint the 6MWD was chosen, which implies that all included patients are still ambulatory. As physical fatigue is one of the major and most limiting symptoms [3], the 6MWD seems to be the ideal endpoint to observe positive effects on muscle function, and to assess fatigue and endurance due to CIT intake. Furthermore, due to the asymmetric nature of the disorder the 6MWD seems to be optimal regardless of whether walking impairment is caused by the right or left proximal or distal leg being affected.

The MFM is a scale used in neuromuscular diseases to assess their severity and progression. It is used by physiotherapists or rehabilitation physicians and is useful to observe motor function changes in clinical trials [29]. The test includes 32 items including specific motor functions such as transfers and standing (D1), proximal and axial (D2) and distal (D3). The total MFM score involves all the motor dimensions [18] and can, therefore, also detect motor function changes in body parts which are not involved in walking and are not evaluated in the 6MWD.

In order to increase sensitivity and to detect subclinical positive effects on muscle mass and muscle metabolism, quantitative muscle MRI (qMRI) is performed. We and others have demonstrated that qMRI is more sensitive than clinical evaluation and visual analysis of MRI scans and it also shows an excellent reproducibility [20, 21, 24]. qMRI is a powerful technique to evaluate neuromuscular and muscular disorders in a noninvasive way for evaluation of disease progression and, furthermore, it is a good biomarker in clinical trials [30]. Kinali et al. showed a good correlation between muscle histology and MRI changes in patients with DMD [31]. Furthermore, to investigate ATP in human muscle in vivo, ^31^P-MR spectroscopy is used (during rest, exercise and recovery). With this method, the mitochondrial function and the regeneration of ATP after muscle exercise could be investigated.

### Trial status

The trial started enrolment in June 2016 and is expected to be completed by the end of August 2017.

## Abbreviations

^31^P-MR: Phospho-magnet resonance
4-HNE: 4-Hydroxynonenal
6MWD: 6-min Walking Distance Test
8OHDG: 8-hydroxy-2’-deoxyguanosine
ATP: Adenosintriphosphate
BMD: Becker muscle dystrophy
BSD: Big Stick Design
cGMP: Guanosine 3’,5’-monophosphate
CIT: L-citrulline
GFR: Glomerular filtration rate
HDL: High-density lipoprotein
IBM-FRS: Inclusion Body Myositis Functional Rating Scale
IDEAL-CPMG: Iterative Decomposition of water and fat with Echo Asymmetry and Least-squares estimation-Carr-Purcell-Meiboom-Gill
LDL: Low-density lipoprotein
MELAS: Mitochondrial encephalomyopathy, lactic acidosis and stroke-like episodes
MFC: Muscle fat content
MFM: Motor Function Measurement
MRI: Magnetic resonance imaging
MTI: Maximum tolerated imbalance
NO: Nitric oxide
NOS: Nitric oxide synthase
PCr: Phosphocreatine
PGC-1α: Peroxisome proliferator-activated receptor-γ coactivator 1α
PPS: Post-polio syndrome
qMRI: Quantitative magnetic resonance imaging
SIPP: Self-reported Impairments in Persons with late effects of Polio rating scale
WHOQOL: The World Health Organisation - Quality Of Life
